## Abstract

**Background:**

Non-alcohol fatty liver disease (NAFLD) is the most common chronic liver disease in the world, with a high incidence and no effective treatment. At present, the targeted therapy of intestinal microbes for NAFLD is highly valued. *Lycium barbarum polysaccharide* (LBP), as the main active ingredient of Lycium barbarum, is considered to be a new type of prebiotic substance, which can improve NAFLD by regulating the gut microbiota. The purpose of this study is to evaluate the safety and efficacy of LBP supplementation in modulating gut microbiota for NAFLD patients.

**Methods:**

This randomized, double-blind, placebo-control study will be conducted in the physical examination center of the Ningxia Hui Autonomous Region People’s Hospital. A total of 50 patients with NAFLD confirmed by abdominal ultrasound, laboratory tests, and questionnaire surveys will be recruited and randomly assigned into the control group (maltodextrin placebo capsules) and the intervention group (LBP supplementation capsules) for 3 months. Neither patients, nor investigators, nor data collectors will know the contents in each capsule and the randomization list. The primary outcome measure is the level of ALT concentration relief after the intervention. Secondary outcomes include gut microbiota abundance and diversity, intestinal permeability, patient’s characteristic demographic data and body composition, adverse effects, and compliance from patients.

**Discussion:**

LBPs are potential prebiotics with the property of regulating host gut microbiota. Our previous studies have documented that LBP supplement can improve the liver damage and the gut microflora dysbiosis in NAFLD rats. This treatment would provide a more in-depth understanding of the effect of this LBP supplementation.

**Trial registration:**

Chinese Clinical Trial Register, ChiCTR2000034740. Registered on 17 July 2020.

**Supplementary Information:**

The online version contains supplementary material available at 10.1186/s13063-021-05529-6.

## Background

Non-alcoholic fatty liver disease (NAFLD) is characterized by the presence of fat accumulation more than 5% in hepatocytes, which is not due to hepatitis B virus (HBV) or hepatitis C virus (HCV) infection and excessive alcohol consumption. It is a chronic and wide spectrum of liver disease, involving a complex progression from simple steatosis to non-alcoholic steatohepatitis (NASH) and then to cirrhosis, hepatocellular carcinoma, even lead to liver transplantation and death [1]. Over the past few decades, the estimated incidence and prevalence of NAFLD has risen dramatically globally due to dramatic changes in lifestyle and the improvement of living standards. According to a systematic review and meta-analysis, no matter what diagnostic method was used, the global prevalence of NAFLD was 29.62% [2, 3]. NAFLD primarily associated with low physical activity levels, central obesity, diabetes, hypertension, and metabolic syndrome has become an important public health issue [4]. However, the mechanism of pathogenesis and progression of NAFLD is multifactorial and complex and there are no approved pharmacological therapies for the treatment of NAFLD up to now [5].

It is well known that the liver and intestine have anatomical links through the hepatic portal system, the gut microbiota and its metabolites may be involved in the pathogenesis of liver disease, and the gut-liver axis is increasingly recognized as a key player [6]. The gut epithelium is a natural physical barrier that prevents the translocation of detrimental gut bacteria and their metabolic by-products into the blood [7]. It was documented that high fat diets could lead to microbiota dysbiosis and the gut barrier dysfunction, which increase intestinal permeability and allow the bioproducts of gut microbiota such as LPS to enter the portal circulation [8]. Lipopolysaccharide (LPS), the active component of endotoxin, is the main gut-derived metabolites that may be involved in the pathogenesis of NAFLD. Serum increased LPS combined the Toll-like receptor 4 (TLR-4) complexes and subsequently stimulating the production of inflammatory reaction and insulin resistance in the liver [9]. Therefore, gut microbiota is an important environmental factor involving the pathogenesis of NAFLD.

Probiotics are defined by the Food and Agriculture Organization and World Health Organization (FAO/WHO) as a collection of living microorganisms that are beneficial to the host metabolism [10, 11]. Several studies have reported the probiotic supplementation could restore the gut microbiota structure and intestinal barrier integrity [12]. Ma et al. [13] performed a meta-analysis evaluating the effect of probiotics on NAFLD, demonstrating that probiotics significantly improved NAFLD by reducing the levels of serum ALT, AST, LPS, and liver TNF-α, TLR4. Studies from Li et al. [14] suggested that probiotics could enhance the barrier integrity of epithelial cells and restore normal gut flora structure and proportion, which reduces the liver injury of NAFLD. *Lactobacillus* and *Bifidobacterium* are the most commonly used symbiotic or probiotics, which can inhibit harmful bacteria growth and have a wide range of benefits on human health [15]. They are naturally contained in common foods, fruits, and tea. In conclusion, regulating enteric flora by probiotics or prebiotics may be a new therapeutic approach for the prevention and treatment of NAFLD [16].

Lycium barbarum (Solanaceae), also called Goji berry or wolfberry, is a well-known traditional Chinese herbal medicine and functional food for many years. It was found mainly in northwest China and has gained an increasing popularity due to its effect in nutritional and health-promoting properties. Goji berries are rich in polysaccharides and one of the most functional active components of wolfberry is *Lycium barbarum polysaccharides* (LBPs) [17]. In recent years, the health benefits of LBP have been reported more and more frequently, such as antioxidant, lipid-lowering, hepatoprotective, neurological protective, and vision-protective. Furthermore, LBP exerts promote effects on the proliferation of “good” bacterium that can be used as a new kind of probiotics which was detected by Fang Zhou et al. [18]. Recent study from Zhu et al. [19] also found that LBPs from Goji berry have prebiotic activities which can stimulate beneficial bacteria growth in vitro, also balancing the microbial composition in gut, enhancing the bacteria concentration and immunity in mice. These results indicate that LBPs are potential prebiotics with the property of regulating host gut microbiota. Taking these advantages as listed above into account, the LBP protective role on many diseases for example type 2 diabetes mellitus (T2DM), liver injury, Parkinson’s disease, and Alzheimer’s disease has been confirmed [20]. However, little is known about whether LBP is a probiotic on the pathogenesis and progression of NAFLD. Considering the positive results of the studies of probiotic on liver injury and there is no specific and effective drug for NAFLD treatment, the hepatoprotective effect of LBP involving NAFLD deserves further study.

In this study, we postulate that LBP can become an adjunct therapeutic option for NAFLD through modulating the gut microbiota. In this context, we conducted a randomized controlled clinical trial to evaluate whether LBP supplementation can improve gut flora disturbance and liver injury of NAFLD.

## Methods/design

### Aim

The primary aim of this trial is to determine the efficacy of LBP supplements in reducing hepatic injury in patients with NAFLD compared to the placebo control group. Secondary objectives of this study include investigating the effects of supplementation with LBP on the gut microbiota, intestinal barrier function, body composition, inflammatory cytokines, and the acceptance and safety for the intervention.

### Study design

This is a single-center, two-group (1:1), prospective, randomized, double-blind, placebo-control study. The present protocol was designed in accordance with the Standard Protocol Items: Recommendations for Interventional Trials (SPIRIT) guidelines and completed the SPIRIT Checklist [21] (Additional file 1). Additionally, the whole study design is illustrated in Fig. 1 and a SPIRIT figure is presented in Fig. 2.

**Fig. 1 Fig1:**
[figure not shown]
Study design. NAFLD: non-alcoholic fatty liver disease; HOMA-IR, homeostasis model assessment for insulin resistance; INS, insulin; FBG, fasting blood glucose; IPAQ, International Physical Activity Questionnaire-Short Form; SpO_2_, oxygen saturation; BP, blood pressure; HR, heart rate; SCFAs, short chain fatty acids

**Fig. 2 Fig2:**
[figure not shown]
SPIRIT figure: schedule of enrolment, interventions, and assessments

This randomized controlled clinical trial has been approved (2019-329) by the Institutional Ethics Committee of Ningxia Medical University, and it has been registered at the Chinese Clinical Trial Registry (ChiCTR2000034740).

### Study participants

All patients with NAFLD treated at the physical examination center of the Ningxia Hui Autonomous Region People’s Hospital will be recruited and invited to participate. The specific inclusion criteria are (1) subjects diagnosed with NAFLD through the abnormal liver enzymes and ultrasonography, (2) aged 45~59 years, and (3) willing to participate in the study and sign informed consent. Patients will be excluded if they have (1) acute or chronic viral hepatitis, drug-induced liver disease, liver cirrhosis, or other causes of chronic liver disease; (2) alcohol consumption > 140 g/week in men or > 70 g/week in women over the past 6 months; (3) intestinal diseases or other chronic inflammation; and (4) diabetes or uncontrolled cardiovascular disease. Other exclusion criteria include regular intake of probiotic supplements or food within 3 months, pregnancy, and use of medications such as corticosteroid drugs, immunosuppressants, and antibiotics.

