### Intervention

According to the inclusion and exclusion criteria, all eligible patients will be introduced to the study. After investigators comprehensively review the inclusion and exclusion criteria and explain the purpose, benefits, and potential risks of the study, patients who agree to participate will be asked to sign an informed consent form (Additional file 2) and then be included in the study. At the baseline, participants will be randomized to allocate an intervention group or a control group. Patients assigned to the intervention group will receive an LBP supplementation capsule and those assigned to the control group will receive an identical appearance capsule containing maltodextrin as the placebo. In this study, the capsules are provided by Ningxia Wofu Bairui Biological Food Engineering Co., Ltd. The concentration of LBP supplementation capsules is 40% and the specification is 0.75 g per capsule. According to the recommended amount, patients will be instructed to take two capsules daily for 12 weeks and not to change their diet or daily physical activity. Follow-up assessments will be performed every 4 weeks at weeks 4, 8, and 12 after randomized allocation. The trained researcher will successively include patients until the target sample size is reached and the project manager will assign participants to interventions according to the randomization list. In general, both LBP supplementation and maltodextrin placebo are considered safe interventions without severe side effects for participants [20]. If any undesirable event occurs (bleeding, allergic and anaphylactic reactions, interactions with other prescriptions, etc.) or the participant requests to withdraw, the investigator can discern whether the trial should be continued. All reasons for terminating the trial will be recorded by the data collector.

There are many strategies that will be used to assess and improve patient compliance. Before administering the intervention, the baseline data of the participants will be generated and gathered. The investigator will detail the duration of the intervention, possible adverse effects, and provide capsules for a period of 4 weeks. The adherence will be assessed by checking the number of remaining capsules and a capsule intake questionnaire at each follow-up visit. At the same time, patients will obtain another set of capsules (every 4 weeks).

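### The 3-month exclusion names probiotics but not LBP, goji products or other prebiotics, so existing users can enter and continue in both arms, with possible dilution of the contrast

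*Protocol article*

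**What the plan says.** Study participants gives the intake-related exclusions in one sentence: "Other exclusion criteria include regular intake of probiotic supplements or food within 3 months, pregnancy, and use of medications such as corticosteroid drugs, immunosuppressants, and" one further drug class. The part that concerns products acting on the gut flora is limited to "regular intake of probiotic supplements or food within 3 months".

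The Background describes the test substance in two ways. It concludes that "LBPs are potential prebiotics with the property of regulating host gut microbiota", in line with the Abstract, which also calls LBP a prebiotic. It also says that LBP "can be used as a new kind of probiotics". Earlier in the same section, probiotics are defined as living microorganisms, which a polysaccharide is not.

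On the source, the Background says that goji "is a well-known traditional Chinese herbal medicine and functional food for many years", and continues: "It was found mainly in northwest China and has gained an increasing popularity".

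Recruitment is at a single hospital in the Ningxia Hui Autonomous Region. Under Intervention, "patients will be instructed to take two capsules daily for 12 weeks and not to change their diet or daily physical activity". The same section describes a capsule count and a capsule-intake questionnaire at each follow-up visit.

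**The concern.** The sponsor evidently saw that recent use of products acting on the gut flora could blur this trial, because there is a 3-month look-back. But that look-back names a different class from the one to which the article mostly assigns LBP. A candidate who regularly takes LBP capsules, concentrated goji or another prebiotic supplement meets the written criteria. Once enrolled, that person is told to leave the diet unchanged.

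The mixed terms add a practical problem. A screener who relies on the definition of probiotics would admit an LBP user. A screener who relies on the sentence calling LBP a kind of probiotic would exclude the same person.

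At stake is how a small or null difference would be read, for ALT and for the microbiota. Nothing in the Measurement subsections records goji, LBP or prebiotic intake, and Data analysis provides for an interaction with physical activity but not with background exposure. On the text shown, a weak result could not be examined for prior exposure.

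**Working it through.** **1. What the criterion covers**

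| Product | Named in Study participants? | Class given in the article |
|---|---|---|
| Probiotic supplements or food | Yes, 3 months | Living microorganisms (Background) |
| LBP products | No | Prebiotic (Abstract, Background); once called a kind of probiotic (Background) |
| Goji as food | No | Functional food, source of LBP (Background) |
| Other prebiotics | No | – |

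**2. How exposure would act**

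Let p be the share of participants who are habitual users, and r the proportion by which their response to added LBP is reduced. With 1:1 randomisation, p is the same in both arms on average, and with diet held constant it stays so. The expected between-arm difference is then

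difference = 6.9 × (1 − f), with f = p × r.

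If r = 0, stable background intake leaves the difference unchanged. The contrast shrinks only if r > 0, or if LBP or goji products are taken off study during the 12 weeks, particularly by the placebo arm.

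**3. The plan's own sample size**

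Inputs from Sample size calculation: ALT falls of 11.3 and 4.4, 90% power, two-sided 5%, 42 patients in total (21 per arm at 1:1), 50 enrolled (25 per arm). The planned difference is 11.3 − 4.4 = 6.9.

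No SD is stated, so 42 cannot be reproduced from the article's inputs alone. Solving a two-sample t test backwards (21 per arm, 40 degrees of freedom, 90% power) gives a standardised difference of 1.025, so

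SD = 6.9 / 1.025 ≈ 6.73.

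The normal approximation gives a total of 42 for SDs from about 6.73 to 6.90, which agrees.

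**4. Illustration of dilution**

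The documents give neither p nor r. Assumed values: p = 10% with r = 50% gives f = 5%; p = 20% with r = 50% gives f = 10%; p = 20% with r = 100%, or p = 40% with r = 50%, gives f = 20%. Two-sided t test, SD 6.73:

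| f | Difference | 20 per arm (50 less 20%) | 21 per arm (planned minimum) | 25 per arm (all enrolled) |
|---|---|---|---|---|
| 0% | 6.90 | 0.885 | 0.90 | 0.94 |
| 5% | 6.56 | 0.85 | 0.87 | 0.92 |
| 10% | 6.21 | 0.81 | 0.83 | 0.89 |
| 20% | 5.52 | 0.715 | 0.74 | 0.81 |

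The 25-per-arm column assumes complete data; imputed values do not carry full information.

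**The case against.** The strongest reply is that the stated aim is LBP supplements compared with placebo, and the Background speaks of an adjunct option. On that reading, the increment from capsules over usual diet is the question being asked, and a placebo arm that eats some goji does not contradict it. Randomisation also balances habitual intake. Both points stand.

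A reader might therefore go too far in three ways:

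- That the comparison is biased toward no difference. This does not follow. It needs a reduced response in exposed people or off-study use, and the documents support neither as fact.
- That the trial compares LBP with no LBP, so the placebo arm is invalid. The Aim section does not say so.
- That intake can never be checked. Figures 1 and 2 and the additional files are not shown, the items of the capsule questionnaire are not listed, and the Abstract mentions questionnaire surveys without giving their content. A dietary item could be there.

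It can also be said that the probiotic wording was meant to reach LBP, since the Background once uses that term for it. That is possible, but it is a reason to make the wording explicit, and it would still leave ordinary goji eating unaddressed. Finally, that Ningxia lies in the goji region is an inference from the Background and the site's location, not a statement in the article.

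**Conclusion.** The eligibility text has a real gap and an inconsistency of terms. As written, it can admit people who already take the test substance or others of its class, and the diet instruction lets them continue. The consequence is possible dilution, not imbalance and not demonstrated bias.

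Its size is unknown. The fall in power to about 87% to 74% at 21 per arm (92% to 81% with all 25 analysed) rests on an assumed loss of 5% to 20% of the contrast and on an SD the plan does not state. The gap in the wording does not depend on those figures. The change is worth making because it is cheap, and because exposure that is never recorded cannot be allowed for in the analysis.

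**What to change.** 1. In Study participants, extend the 3-month criterion to regular intake of LBP or concentrated Lycium barbarum products and of other prebiotic supplements, and use the terms probiotic and prebiotic consistently.
2. In Intervention, state that these products are not taken outside the study capsules until the week-12 samples have been collected.
3. Record ordinary goji and prebiotic intake at baseline, and at each visit by adding an item to the existing capsule questionnaire. Excluding everyone who eats goji as ordinary food would narrow the trial's applicability to the local population, so recording intake is the better course there.
4. Plan a sensitivity analysis by habitual intake. Trial status says recruitment is under way, so ask those already enrolled about their intake and include them.

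Cost: a short amendment and one questionnaire item. A few otherwise eligible candidates are lost, which Recruitment suggests is affordable, since it describes the yearly patient numbers as sufficient. With 25 per arm, the sensitivity analysis will have low power and should be read as descriptive.

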### Intervention

According to the inclusion and exclusion criteria, all eligible patients will be introduced to the study. After investigators comprehensively review the inclusion and exclusion criteria and explain the purpose, benefits, and potential risks of the study, patients who agree to participate will be asked to sign an informed consent form (Additional file 2) and then be included in the study. At the baseline, participants will be randomized to allocate an intervention group or a control group. Patients assigned to the intervention group will receive an LBP supplementation capsule and those assigned to the control group will receive an identical appearance capsule containing maltodextrin as the placebo. In this study, the capsules are provided by Ningxia Wofu Bairui Biological Food Engineering Co., Ltd. The concentration of LBP supplementation capsules is 40% and the specification is 0.75 g per capsule. According to the recommended amount, patients will be instructed to take two capsules daily for 12 weeks and not to change their diet or daily physical activity. Follow-up assessments will be performed every 4 weeks at weeks 4, 8, and 12 after randomized allocation. The trained researcher will successively include patients until the target sample size is reached and the project manager will assign participants to interventions according to the randomization list. In general, both LBP supplementation and maltodextrin placebo are considered safe interventions without severe side effects for participants [20]. If any undesirable event occurs (bleeding, allergic and anaphylactic reactions, interactions with other prescriptions, etc.) or the participant requests to withdraw, the investigator can discern whether the trial should be continued. All reasons for terminating the trial will be recorded by the data collector.

There are many strategies that will be used to assess and improve patient compliance. Before administering the intervention, the baseline data of the participants will be generated and gathered. The investigator will detail the duration of the intervention, possible adverse effects, and provide capsules for a period of 4 weeks. The adherence will be assessed by checking the number of remaining capsules and a capsule intake questionnaire at each follow-up visit. At the same time, patients will obtain another set of capsules (every 4 weeks).

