### Laboratory assessment and imaging

Laboratory investigations include liver enzymes (γ-glutamyltransferase (GGT), alanine aminotransferase (ALT), and aspartate aminotransferase (AST)); biochemical markers of lipogenesis such as triglycerides (TG), total cholesterol (TC), LDL-cholesterol, HDL-cholesterol, and free fatty acids (FFA); and inflammatory factors (IL-6, IL-1β, TNF-α, MCP-1). At baseline and 12 weeks, the blood sample will be collected for laboratory evaluation after a 12-h overnight fasting. Liver enzymes and lipid profiles (TG, TC, LDL-cholesterol, HDL-cholesterol) will be measured by an automatic biochemistry analyzer. The levels of FFA will be assayed using an FFA assay kit (Nanjing Jiancheng Bioengineering Institute, Nanjing, China). Gas chromatography-mass spectrometer (7890B-5977A GC/MSD, Agilent, USA) will be used for the short chain fatty acids (acetic acid, propanoic acid, butyric acid, isobutyric acid, N-valeric acid, isobutyric acid, caproic acid) analysis. The concentration of inflammatory factors will be determined by enzyme-linked immunosorbent assays (ELISA) kit (Elabscience Biotechnology Institute, China). All laboratory assessments will be performed in the same laboratory by using standard laboratory methods. At the beginning and the end of the intervention period, ultrasound examination of the abdomen will be performed on all patients, and the hepatic steatosis will be noted and graded.

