## Outcome measures

### Primary outcome measure

The primary outcome measure will be a significant ALT concentration relief after the intervention, which is assessed and recorded by the researchers according to the results of laboratory assessment.

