### Sample size calculation

Based on the previous study results of supplementing synbiotics in NAFLD, this study took the significant reduction of ALT concentration as the main outcome indicator for sample size calculation. According to the research of Eslamparas et al. [23], it was found that the concentration of ALT decreased 11.3 and 4.4 in the intervention and control groups respectively. It aimed to determine an appropriate target sample size that would provide a 90% power (*β* = 0.10) for two-tailed testing with 5% type-1 error rate of the measure. Using the PASS 22.0 software, we calculated a minimum requirement of 42 patients for total. In practice, we decided to enroll a total of 50 participants (*n* = 25 per group), taking into account the 20% drop-out rate before the end of the study.

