### Participant retention and withdrawal

Once the participants are registered, the research team has the responsibility to achieve a low rate of loss to intervention. Before the start of the intervention, investigators will conduct education, detailing the duration of the intervention and possible adverse effects. During the intervention and follow-up period, the trained researchers will remind the subjects to take the capsules, fill in the capsule taking record form, ask if there is any uncomfortable, and give psychological support to participants.

All patients will be informed that they have the right to withdraw from the study at any time during the intervention and the Data Monitoring Committee (DMC) will discuss and analyze the reasons for dropouts with data collectors, which will be documented in a standardized proforma.

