### Data analysis

All patients randomized should be included in the analysis and missing data will be handled using multiple imputation. The test data will be analyzed by a statistical expert using SPSS version 22.0 (Chicago, IL, USA). The statistical expert is not involved in the experiment and is only responsible for the analysis of the data. We will use descriptive statistical methods to measure demographics and baseline clinical features. The categorical variables will use the chi-square test or Fisher’s exact test for analysis and are reported as numbers and percentages. The numerical variables will be reported as mean±standard deviation or medians with interquartile ranges (IQR) comparing by Student’s *t* test or the Mann-Whitney *U* test. Ranked data will be analyzed using the rank-sum test. Follow-up data will be compared using the repeated measures analysis of variance (ANOVA). A multiple linear regression method was used to establish a linear equation of multiple linear regression to detect the interaction between the amount of physical activity and the efficacy of LBP supplements.

The alpha and beta diversity of the gut microbiota will be estimated by MOTHUR and QIIME at the OUT level, respectively. Sample cluster will be conducted by QIIME based on UPGMA. KEGG and COG functions will be predicted using the PICRUSt software. Barplot and heatmap of different classification levels will be plotted with T package v3.4.1 and R package “gplots”, respectively. Cases with missing values in the resulting parameters will be excluded from the analysis. All results are statistically significant with *P*<0.05.

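### The plan does not separate stopping the capsules from leaving follow-up, so the single post-baseline ALT may be lost for participants who stop early

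*Protocol article*

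**What the plan says.** All references are to the protocol article.

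- **Intervention.** After an undesirable event or a request to withdraw, "the investigator can discern whether the trial should be continued". The next sentence adds: "All reasons for terminating the trial will be recorded by the data collector". No option is described in which a participant stops the capsules but stays in follow-up.
- **Intervention, visits.** "Follow-up assessments will be performed every 4 weeks at weeks 4, 8, and 12 after randomized allocation". Visits are therefore timed from randomisation, not from time on capsules.
- **Participant retention and withdrawal.** Participants are told that "they have the right to withdraw from the study at any time during the intervention". Withdrawal here is from the study.
- **Laboratory assessment and imaging.** "At baseline and 12 weeks, the blood sample will be collected for laboratory evaluation after a 12-h overnight fasting". No ALT sample is described at weeks 4 or 8.
- **Primary outcome measure.** "The primary outcome measure will be a significant ALT concentration relief after the intervention".
- **Sample size calculation.** The enrolment of 50 was set "taking into account the 20% drop-out rate before the end of the study".
- **Data analysis.** "All patients randomized should be included in the analysis and missing data will be handled using multiple imputation". A later sentence in the same section, placed after the microbiota methods, excludes cases with missing values in the resulting parameters. Whether it covers ALT is unclear.

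**The concern.** The article does state a rule for what follows an adverse event or a withdrawal request, and that rule has one object: continuing or terminating the trial. Stopping treatment and ending observation are different events. The first need not remove a participant from an analysis of everyone randomised; the second usually does.

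This design is exposed because ALT has a single post-baseline sample. A participant terminated at week 3 or week 9 contributes nothing after baseline to the primary outcome. With no intermediate ALT, a standard missing-at-random imputation would draw on baseline data and on participants who reached week 12, most of them still taking capsules. If people stop because of intolerance or lack of benefit, their values would be filled in as though treatment had continued. If they were excluded instead, the comparison would be among completers. In both cases the result would be reported for all randomised patients without having observed all of them.

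**Working it through.** **Inputs from the article**

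- ALT decrease 11.3 (intervention) and 4.4 (control): difference 11.3 − 4.4 = 6.9 (Sample size calculation).
- 50 participants, 25 per arm, 20% drop-out: 0.20 × 50 = 10 primary values at risk, leaving 40 (20 per arm if losses are equal).
- ALT at baseline and week 12 only (Laboratory assessment and imaging).

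**The plan's own figure.** The minimum of 42 cannot be confirmed, because no standard deviation is given. Solving backwards for 90% power, two-sided 5%, 21 per arm gives an SD of 6.73 with the t-test (about 6.9 with the normal approximation). The bias calculation below does not depend on the SD.

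**Assumptions not in the article**

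- q: share of the LBP arm that stops early. Range 10% to 20%, the upper end set equal to the planned drop-out.
- k: share of the benefit that a stopper keeps at week 12. Range 0 to 0.5.
- Stopping placebo does not change the control mean.
- Unmeasured values are filled from completers, whose difference is 6.9. Excluding the stoppers gives the same expected 6.9.

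**Formula.** All-randomised effect = 6.9 × (1 − q) + 6.9 × q × k. Overstatement = 6.9 / (all-randomised effect) − 1.

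| q | k | All-randomised effect | Overstatement by 6.9 |
|---|---|---|---|
| 10% | 0.5 | 6.21 + 0.345 = 6.555 | 5% |
| 10% | 0 | 6.21 | 11% |
| 20% | 0.5 | 5.52 + 0.69 = 6.21 | 11% |
| 20% | 0 | 5.52 | 25% |

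**Does measuring the stoppers raise power?** Assume an SD of 6.7, close to the back-solved value, and a two-sample t-test.

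- 20 per arm, all completers, difference 6.9: power about 89%.
- Half of the lost samples recovered (22 or 23 per arm), no benefit kept by those recovered: the difference is 6.9 × 20/22 = 6.27 or 6.9 × 20/23 = 6.00, and power is about 86% or 84%.
- All 25 per arm measured, no benefit kept: the difference is 6.9 × 20/25 = 5.52 and power is about 81%.
- Half the benefit kept, 22 to 25 per arm: power stays at about 89%.

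Power rises above 89% only if those who stopped keep most of the effect (about 92% or 93% at 22 or 23 per arm with the full 6.9). That assumption removes the bias. In the scenarios that produce the bias, power does not rise.

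**The case against.** **The article does not say that stoppers go unmeasured.** This is the strongest objection, and it stands against a tempting stronger reading: that stopping capsules ends participation, so week-12 ALT is necessarily lost. Visits run from randomisation, and leftover capsules are counted at each visit, so following non-takers is compatible with the text. The fuller protocol or the schedule figure, neither of which I could consult, may settle it. What remains is that the rule the article does give has only one outcome, continue or terminate, and a site reading it literally could stop collecting data.

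**It belongs in the analysis plan.** This does not stand. Whether blood is drawn at week 12 is a conduct rule, and no analysis plan can recover a sample that was never taken.

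**The imputation model is not specified.** This stands in part. The article does not say what the imputation conditions on, and adherence data from weeks 4 and 8 could inform it. Nor does an all-randomised analysis with multiple imputation become contradictory because outcomes are missing. What matters is whether missing-at-random is credible, and that cannot be judged here. The later exclusion sentence also leaves it uncertain whether ALT would be imputed at all.

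**The size is assumed.** This stands. The 20% is drop-out from the study, not capsule stopping in the LBP arm, and some of those people would refuse follow-up under any rule. The article also describes both capsules as safe, which gives little support to intolerance as a common reason for stopping.

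**A power gain might be inferred.** A reader might expect recovered samples to raise power. The calculation above does not support this in the scenarios that cause bias.

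**Conclusion.** The point holds in a limited form. The discontinuation rule under Intervention does not distinguish stopping capsules from leaving follow-up. With one post-baseline ALT sample, anyone terminated early has no primary outcome. The all-randomised analysis then depends on imputation, or on exclusion, for up to about 10 of 50 participants at the planned drop-out.

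If values are in effect taken from completers, 6.9 would overstate the all-randomised difference by about 5% to 25%. This rests on 10% to 20% of the LBP arm stopping and keeping half or none of the benefit, on no change in the control mean, and on those people being willing to be measured. If stoppers keep their benefit, there is no overstatement. The figures illustrate what is at stake and do not predict the bias. The case for change rests on bias alone. It is worth acting on because the remedy is cheap and has to be in place before samples are missed.

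**What to change.** 1. Under Intervention, separate two events: stopping the capsules, and withdrawing consent for follow-up. The decision to stop capsules stays with the investigator.
2. State that anyone who stops capsules for any reason is still invited to the scheduled week-12 visit for ALT and the other assessments, and is analysed in the arm to which they were randomised.
3. Record the reason for stopping capsules separately from the reason for leaving follow-up.
4. Reserve multiple imputation for participants who refuse the week-12 visit or cannot be reached.
5. Reconcile the two missing-data sentences under Data analysis. If exclusion applies only to the microbiota analyses, say so.

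The cost is a few sentences and at most about 10 week-12 visits, already planned for all 50 participants. The estimated effect may be smaller than among completers, but it would then describe everyone randomised. Participants who decline follow-up remain unmeasured, so some reliance on imputation would continue.
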